# Background

Osteoarthritis (OA) is a chronic condition affecting the joints of older people. It is often associated with functional limitation and persistent pain, both of which can impact on mood and quality of life. OA is one of the most common reasons for primary care consultation in the UK, with approximately 1 million seeking treatment each year [1]. Despite it being a prevalent disorder the ability to effectively treat and maintain an improvement in OA symptoms in primary care is limited [2]. One reason for this may be that the majority of prognostic indicators for the course of OA are not modifiable (e.g. age, gender and symptom duration). One potentially modifiable factor associated with the outcome of OA is depressive symptoms [3]. In individuals with persistent pain conditions, such as OA, depression has been shown to occur up to four times more frequently than in individuals without persistent pain [4-6]. Furthermore, the results of a randomised controlled trial showed that treating major depression in patients with OA resulted in improvements in OA outcomes, including pain and function, and quality of life [7,8]. However, the detection of depressive symptoms in primary care is poor, particularly in those patients with a chronic physical illness [9,10]. Depressive symptoms that do not reach criteria for major depression, often termed “sub-threshold” or “mild” depression, are still considered to be distressing and disabling, particularly for patients with a chronic disease such as OA, and stepped care of “active monitoring” or treatment is recommended [11].

Screening for depression as a routine assessment endeavours to improve identification of depressive symptoms, and consequently facilitate implementation of the management of depressive symptoms. Screening for depressive symptoms during primary care consultations for diabetes and coronary heart disease patients, using two brief questions [12], has been stipulated as part of the Quality Outcomes Framework for UK primary care practice since 2006. Indeed, screening and subsequent treatment of depressive symptoms in patients with diabetes has been shown to be associated with healthcare cost savings [13], and it is likely that a similar finding would be observed in this trial, amongst patients with OA. Recent literature reviews have recommended that such screening is also carried out in high risk groups with comorbid medical conditions [14,15], including chronic painful conditions [9,16]. The American College of Preventative Medicine goes as far as to state that primary care providers should screen all adults for depression [17], yet in order for screening to be beneficial, evidence suggests that effective systems for the diagnosis, treatment and management of depression should be in place [18,19]. Such recommendations for depressive symptom screening have now been included in the National Institute for Clinical Excellence (NICE) guidelines for holistic OA management [20]; however, the extent of their implementation is yet to be ascertained. NICE guidelines for depression in adults with a chronic physical health problem [11] give details of how such comorbid depressive symptoms should be identified, treated and managed [21]. Ultra-short screening tools (two to three items) have been shown to be useful at identifying up to eight out of 10 probable cases of depression with a high false positive rate noted [22]. However, screening is accepted as a method of identifying depressive symptoms that warrant a subsequent more detailed assessment to determine their severity [11,22]. A recent study that used the 2-item depression screen in patients with musculoskeletal pain supported these findings [23], highlighting the importance of detecting depressive symptoms in chronic pain patients, even those that are considered to be sub-threshold or mild symptoms, rather than just screening for diagnosable depressive disorders. This observational study of 428 patients aged 50 years and older consulting with non-inflammatory musculoskeletal pain found that 18.2% (n=78) screened positive for depression using the PHQ-2 [23]. It is unlikely that screening by itself will result in improved symptoms of either depression or pain, rather it is anticipated that identification of depressive symptoms would result in altering care to address and, where appropriate, initiate treatment, for such symptoms [24]. It is this screening combined with collaborative care of comorbid depressive symptoms that appears to be successful in reducing OA related symptoms [7,8]. However, screening continues to be recommended in clinical guidelines [20], yet how beneficial such a screening and subsequent modification of care approach is for OA patients with sub-threshold or mild depressive symptoms has yet to be determined.

The majority of work concerning comorbid mood disorders in primary care, has investigated depression, however, anxiety has been shown to be common in primary care patients (14.6% to 19.5%) [25,26]. Similarly, evidence suggests that anxiety might be more common than depression amongst patients with OA (e.g. 46.4% vs. 29.2% [27]; 48.9% vs. 26.5% [28]; 44.7% vs. 34.5% [29]. However, less than half of anxious cases are estimated to be recognised by their GP [27]. It is common for anxiety to lead to the development of depression [30] or co-occur with depressive symptoms [31] in primary care patients; and to have a potentially negative impact on well-being [32]. Consequently, screening for anxiety symptoms in OA primary care patients has been recommended as the first step in improving patient outcomes [20] and to help prevent the development of depressive disorders [33,34]. The recent development of a 2-item screening tool for generalised anxiety disorder (GAD-2) [26] also efficiently screens for three other common anxiety disorders (panic disorder, social anxiety disorder, and posttraumatic stress disorder) and is suitable to detect anxiety symptoms in patients across a continuum of anxiety symptoms.

We shall undertake a cluster randomised trial that prompts the recommended holistic assessment of OA [20] by screening for both anxiety and depression in an OA primary care population. This will allow us to determine the effectiveness of screening in terms of an improvement in pain related outcomes and additionally allow us to determine the cost effectiveness of such a screening intervention, as recommended in a recent systematic review of literature regarding screening for depression in primary care [35]. There is growing evidence of the futility of screening for depressive symptoms and disorders in the primary care setting without an intensive collaborative care treatment plan in place [36,37]. Nevertheless, screening for “case finding” is recommended in the GP contract for patients with chronic heart disease and diabetes [38]; it is also recommended in NICE guidelines for patients with a chronic physical health problem [11]. However, it is important to emphasise that this trial is not intended to instigate a system of case-finding and management of major depressive or anxiety disorder requiring a highly complex intervention incorporating the provision of best-evidence treatment for these disorders; rather we are interested in the effect on OA care and outcomes of introducing structured prompts to alert GPs to the possible presence of concurrent depressive and anxiety symptoms as part of a holistic assessment in patients presenting to their GP with clinical OA or peripheral joint pain.

# Aims

The overall aim of this trial is to develop and test a systems intervention to prompt holistic OA treatment in primary care; first and foremost with the recognition of concurrent depressive and anxiety symptoms. This will allow us to investigate whether routinely incorporating brief screening questions for depressive and anxiety symptoms in OA patients results in an improvement in their OA care and outcomes. The clinical and cost-effectiveness of such an intervention compared to a control arm of usual care will be investigated.

## Primary objective

The primary objective of the trial is to determine whether screening for generalised anxiety and depressive symptoms in patients who consult their GP with OA or peripheral joint pain results in an improvement in their pain-related outcomes. Specifically, we hypothesise that patients who are screened for depressive and anxiety symptoms in their GP consultation will have an improvement in their self-reported current pain intensity and pain interference with daily activity ratings (numerical rating scale 0-10) over the 12 months following their consultation, compared to patients in the control arm. Growth curve models will be used to summarise the pattern of response over time between the groups. Changes in slope and intercept will reflect differences in rate of change and mean scores over the 12 months.

## Secondary objective

A secondary objective of the trial will be to evaluate the cost utility of screening for depressive and anxiety symptoms in patients with OA.

# Methods/Design

This study is designed as a cluster randomised controlled trial with two arms. Both arms will ask a standard set of questions during the consultation; however, the content of the template will vary between the two trial arms. The template in the intervention arm will include a total of five questions (two each for depression and anxiety screening, and a fifth question on pain intensity), the template for the control arm will include only the one question on pain intensity; further details of the screening template are provided below. It is termed as a “systems” intervention to incorporate both the screening template and subsequent approach to treatment that the GP follows. The treatment itself will not be implemented as part of the trial protocol; instead the recommended treatment course will be reinforced with GPs in the intervention arm prior to the study commencing (further details provided below). A summary of the study design is illustrated in Figure 1.

A cluster randomised trial rather than an individual randomised trial was chosen for both scientific and practical reasons. GPs are likely to find it difficult to act differently towards patients if they were individually randomised to control and intervention arms during the consultation and therefore contamination between the two arms would be likely. This trial can be thought of as a professional-cluster intervention type [39], in that the intervention involves professional activity during consultation and although the patient can opt out of their data being used, the intervention is still likely to have an effect on them since it involves introducing specific questions to an OA/peripheral joint pain consultation. To this extent the intervention or control template has to be introduced at a practice level since it involves using and comparing the outcome from practice level services.

A period of “run-in” will be adopted to ensure that all study procedures run smoothly and according to protocol. Further details of this period are given below.

**Figure 1:** Flowchart of study design

[figure not shown]

***Minimising systematic bias***

The threat of selection and recruitment bias in cluster randomised trials is high [40]. A number of steps have been taken in the design of this trial to minimise these threats:

- All GP practices will be given the same information about the trial prior to randomisation. This will be brief information about the study and will not include specific details of the study hypotheses. By not raising the profile of depressive and anxiety symptom screening prior to randomisation we anticipate that selection bias of GP practices agreeing to take part will be limited as will contamination about anxiety/depressive screening to GPs in practices that are subsequently randomised to the control arm.
- The electronic template will only be active in each GP practice for approximately three months and will apply to all GPs working in that practice. Therefore any extra work that may be considered as a result of the screening template will not fall on only one GP and the relatively short time period will mean that GPs are less likely to preferentially select patient’s based on their work demands.
- The study name was purposely chosen as it does not include any psychological terms; therefore eluding direct information about the study hypotheses, both to GPs and to patients.
- The electronic screening template is designed to automatically “pop-up” when a Read code for OA/peripheral joint pain (from a pre-determined list) is entered onto an eligible patient’s electronic record. This process has worked well in a previous study carried out at this research centre [23]. This method omits any human error on the GP’s part to forget to ask an eligible patient the screening questions.
- If a GP deems a patient as ineligible to take part they will be asked to give a reason for this exclusion before exiting the template. We will be able to audit and monitor template completion within a practice. We will be able to describe the frequency of template non-completion and subsequent non-enrolment into the study. This will give us some insight into the degree to which selection bias may have occurred. This information will be relayed back to GP practices.
- Patients in both arms of the trial will receive identical study information and questionnaires; minimising the threat of recruitment bias.

Further details about these steps to minimise recruitment and selection bias are provided, where appropriate, in the subsequent sections of the protocol.

***Study participants***

Individuals aged 45 years and older who consult their GP with peripheral joint pain or OA (from a designated set of pre-determined Read codes) will form the sampling base for the trial.

*Inclusion criteria:*

- Aged 45 years and over
- Registered with the participating GP practices during the specified study period of that practice
- Read-coded peripheral joint pain or OA consultation within the specified study period (termed the “index consultation”; may be first, new episode, or ongoing consultation)
- Provided full written informed consent to study participation and to further contact

*Exclusion criteria:*

- Patients who are under active care for or who have a diagnosis of depression and/or an anxiety disorder in the past 12 months
- Vulnerable patients, including any patients on the Quality and Outcomes Framework mental health register, or those who have a diagnosis of dementia or a terminal illness
- Patients who reside in a nursing home
- Red flag pathology – recent trauma associated with significant injury; acute, red, hot swollen joint
- Inflammatory arthropathy, crystal disease, spondyloarthropathy and polymyalgia rheumatica

***Recruitment procedure***

*GP Practices*

Approximately 44 “Research Ready” GP practices that use the EMIS consultation system will be recruited through West Midlands Primary Care Research Network (PCRN) (North Cluster). Information given to practices will be general and they will be told that both arms of the trial will ask some questions that are not unlike those already asked as part of best practice primary care, e.g. assessment of pain intensity and depressive symptoms. Information divulged prior to randomisation will be minimal in order to reduce any bias in the practice deciding to take part as they will be told that they have an equal chance of being allocated to either the control or intervention arm. Practices will be selected on the basis of recent research activity, practice demographics and willingness to participate in the study. The GP practices involved in the study will include those from both urban and rural areas, different socio-economic groups and all sizes of practice (based on patient list size and number of GP partners).

When a practice has agreed to take part in the study, the set-up procedure in the practice will involve downloading anonymised patient information on consultation rates for OA, depression, anxiety, and the comorbid rates of these symptoms. An audit of access to psychological services will also be carried out to ensure that they have the resources to run the study adequately. Details of how practices will be randomised to the trial arms and the post-randomisation procedure are given below.

It is anticipated that the template will be active in each GP practice for approximately three months. GP practices will not all be recruited at once, rather recruitment will take place over a one year period and so the template will not be active in all practices at any one time. A service-level agreement will be ascertained with each GP practice, with a small reimbursement included to pay for practice time

*Patients*

Activation of the screening template will result in a “stamp” on the patient’s electronic record, which will allow our informatics team to establish which patients are eligible for entry into the study. This will also be the case for those templates that have not been completed, either because the GP felt the patient was ineligible or because the GP exited the template without completing it. This will allow us to audit the use of the template and to establish the completion rate, however, we will only be able to describe the characteristics of those patients enrolled into the study and who give consent for their medical records to be reviewed. The patient will be given a postcard during the consultation to make them aware that the research team will contact them via the post.

The PCRN informatics team will visit each practice weekly during their specified study period (approximately three months duration) and download the names and addresses of eligible patients into a secure mailing database. No other information, including the answers to the screening questions, will be downloaded until full written consent for study participation and medical record review is received from the patient (collected in the baseline postal questionnaire – see below). Anonymised aggregate age and gender data for all peripheral joint pain/OA consulters during the one month study period will be downloaded. This will allow us to examine differences between those peripheral joint pain/OA consulters without a completed template, either because the patient was deemed ineligible or for unknown reasons, those who have a completed template but do not consent to take part, and those who have a completed template and consent to take part in the study. This will, to some extent, allow us to determine whether any selection bias has occurred.

All eligible participants (from both arms of the trial) will be sent a study pack in the post that contains:

- a letter from their GP practice introducing the study
- a patient information sheet, which outlines the study and includes instructions of what to do if they do or do not wish to take part
- a baseline questionnaire, including a consent form
- a stamped addressed envelope

As recommended by Eldridge et al (2010), the information provided to patients will be the same for both arms of the trial, helping to eliminate contamination bias [39,40]. Following entry of the names and addresses of eligible patients into a secure mailing database (by a member of the PCRN Informatics team), the study pack will be mailed to eligible patients by an administrative assistant at Arthritis Research UK Primary Care Centre at Keele University who will be blinded to cluster allocation. Letters in the study pack will be on GP practice headed paper and will therefore be specific to each practice that takes part in the study. The patient information sheet and questionnaire will include contact details for the Study Coordinator, who can be contacted should the patient have any further questions about the study. The patient information sheet will also include contact details of their local Patient Advisory Liaison service.

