***Blinding***

The Principal Investigator, Trial Statistician and members of the administration team, who input data from the study questionnaires, as well as the GPs, will be blinded to cluster allocation. The Trial Steering Committee and Data Monitoring Committee will also be blinded to cluster allocation unless it becomes absolutely necessary to reveal allocation.

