**Timeline**

The screening template is currently being turned off at the 8 GP practices involved in block 1 of the trial. 5 GP practices in block 2 are currently active. Ideally the GP questionnaires will be distributed to GPs as close to the end of their study period as possible, so that recall inaccuracy and bias are limited. The semi-structured interviews can begin to take place with GPs whose study period has finished any time after ethics approval has been granted. Due to the nature of GP practices participating in blocks and the study actively recruiting until approximately November 2012, these can take place over a period of time, depending on the availability of the interviewer and GPs. Again, ideally they would be conducted soon after a GP practice’s template has been deactivated.

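### GPs are listed as blinded although they deliver the arm-specific template, and the information given to practices before randomisation is in tension with the plan's own safeguard on mood screening

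*Protocol*

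**What the plan says.** On blinding, the protocol names the principal investigator, the trial statistician and the data-entry staff, "as well as the GPs, will be blinded to cluster allocation".

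On information before randomisation, the section Minimising systematic bias sets out a safeguard: "By not raising the profile of depressive and anxiety symptom screening prior to randomisation", the plan expects to limit both selective uptake by practices and contamination of GPs later allocated to control. The study name was chosen without psychological terms for the same reason.

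Under Recruitment procedure, GP Practices, the protocol says practices are to hear that some of the questions in both arms are "not unlike those already asked as part of best practice primary care, e.g. assessment of pain intensity and depressive symptoms". The next sentence says that what is disclosed before randomisation will be kept minimal. For each practice that agrees, set-up includes an anonymised download of consultation rates for OA, depression, anxiety and their overlap. It also includes a check on services: "An audit of access to psychological services will also be carried out".

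**The concern.** There are two separate points.

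The first is a property claimed for the trial that it does not have. GPs decide whether a patient is ineligible, run the consultation and choose the care that follows. A reader who takes the Blinding section at its word would rate the risk of selection bias at entry, and of differences in care beyond the intended intervention, as lower than it is.

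The second is a mismatch between a safeguard and the text that carries it out. The plan limits practice selection and control-arm contamination by keeping mood screening out of view until allocation. Its recruitment wording then names depressive symptoms to every practice. A control GP who has been told this, knows there are two arms and receives a template with one pain question may guess what the other arm is asking. If such GPs then ask about mood more than they otherwise would, the contrast between arms shrinks towards no difference.

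**Working it through.** The Sample size section is not in dispute and no figure changes. The check is a comparison of texts.

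**GP blinding**

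1. *Knowledge of the design.* At recruitment, practices are told that there is a control and an intervention arm and that each is equally likely (Recruitment procedure).
2. *Briefing.* After randomisation every practice meets a research facilitator, who demonstrates its template. Each consulting room gets a crib sheet specific to the arm (Post-randomisation).
3. *Guidance.* Intervention practices receive a presentation and four papers, three of which concern depression or anxiety. Control practices are told to respond to pain ratings as they normally would and receive nothing further on OA best practice (Post-randomisation).
4. *Delivery.* The GP asks the template questions and records the answers (Activation of the screening template). There are five questions in the intervention arm, four of them on mood, and one on pain in the control arm (Methods/Design; Appendix 1).
5. *Eligibility.* GPs apply the exclusion criteria when the template activates (Activation of the screening template). The first criterion is active care for, or a diagnosis of, depression or an anxiety disorder in the past 12 months (Study participants).

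The most generous reading of the Blinding section is that GPs are never given an arm label or told what the other arm contains. Even so, an intervention GP with four mood questions and mood guidelines on the desk, who knows that a control arm exists, is not blinded in any useful sense. Step 5 shows why this bears on bias: a mood-related eligibility judgement is made by someone who can see the arm's content.

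**Information before randomisation**

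1. *Promise.* Specific details of the hypotheses are withheld, and the profile of mood screening is not raised (Minimising systematic bias).
2. *Recruitment text.* Depressive symptoms are one of only two examples given, in a sentence about what both arms ask. Its place directly before the sentence on disclosure ahead of randomisation makes the timing clear enough.
3. *Control template.* It asks only about pain. Read as a description of template content, the statement does not fit that arm.
4. *Set-up steps.* The rate download and services audit are described ahead of the randomisation procedure and apply to every practice that agrees. No feedback of either to GPs is described, but none is ruled out.

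The first half of the promise is kept, since no hypothesis is disclosed and anxiety is not named in that sentence. The second half is weakened.

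**Size**

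No section gives a rate of mood enquiry in control consultations, so the effect on the treatment contrast cannot be calculated. The plan does collect data that would describe it. In Table 2, patients in both arms report at baseline whether the doctor brought up mood at the index consultation.

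**The case against.** The recruitment sentence is hedged. It can be read as illustrating what good primary care already does, not as listing each template's content. Enquiry about depression is already routine for coronary heart disease and diabetes, so a passing mention reveals little. The topic also cannot be wholly hidden from control GPs, because the exclusion criteria they apply name depression and anxiety. All of this stands. It reduces the second point to a tension between sections that should be reconciled. A reader might infer that the hypothesis is disclosed to practices, or that they are told something plainly untrue about the control arm; the text supports neither.

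On blinding, the protocol has partial protections. GPs must give a reason for each exclusion, template completion is audited, aggregate age and sex are compared across groups of consulters, patient materials are identical, and outcomes are mainly self-reported by post. These help to detect or limit bias. They do not make the GPs blinded.

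Three further inferences should be resisted.

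- *A loss of power.* Any such figure needs an assumed contamination rate and assumes that a control GP who guesses the topic delivers the equivalent of the intervention. The plan defines that as a template plus a reinforced approach to treatment, so a guess about the topic falls well short of it.
- *Moving the services audit to intervention practices after allocation.* The audit confirms that a practice can run the study. Doing it late and in one arm would reveal inadequate services in that arm only, and could cause unequal loss of practices.
- *Delaying the control-arm GP interviews.* The substudy's timeline says of the interviews that "ideally they would be conducted soon after a GP practice" has had its template switched off, which falls within patient follow-up. But they come after the index consultations, and the substudy wants prompt timing to limit recall problems. It also compares the arms, and a delay in one arm only would confound that comparison.

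**Conclusion.** The blinding statement is wrong for GPs. This follows from the protocol's own description of what they receive and do, and needs no assumption beyond the ordinary meaning of blinded. It does not extend to the other roles listed in that section. Nor is the lack of GP blinding a design fault: with an intervention delivered by the GP it is unavoidable, and the fault lies in claiming otherwise.

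The recruitment wording conflicts in spirit with the stated safeguard and fits poorly with the pain-only control template. Any resulting contamination would push the result towards no difference, but its size cannot be computed from the document and no estimate is offered. Both points should be corrected. Neither invalidates the design.

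**What to change.** 1. **Blinding section.** Remove the GPs from the list of blinded parties, state that they are not blinded, and acknowledge the resulting risk of selection and performance bias. This costs nothing.

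2. **Recruitment procedure.** For practices still to be recruited, reword the information so that depressive symptoms are not singled out, for instance by referring only to routine questions of the kind good primary care already asks. The substudy timeline describes recruitment continuing to about November 2012, so later blocks could still benefit. The cost is that practices, which consent as guardians for their patients, receive slightly less specific information.

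3. **Set-up steps.** State that the depression and anxiety rate download and the services audit are run identically in all practices, and that results are not fed back to GPs before the practice's study period ends. This keeps the audit's purpose and treats the arms alike.

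4. **Describing contamination.** Use the baseline item on whether the doctor asked about mood to report, by arm, how often this happened. No new data collection is needed.
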